### Statistical analysis

Statistical analyses will be performed using SPSS 17.0 and Microsoft Excel 2007 software. Data will be expressed as mean ± standard deviation. Changes in variables before and after training and between groups will be analyzed. The main analysis will be to compare the efficacy of ITCRP group with the control group, including the primary and secondary outcomes, using 2-way analysis of variance (group × time). We will conduct an intention-to-treatanalysis if participants are lost to follow-up. The basic intention-to-treat principle is that participants in trials should be analyzed in the groups to which they were randomized, regardless of whether they received or adhered to the allocated intervention. Statistical significance was assumed at *P* less than 0.05.

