**Methods/Design:**

We will conduct a prospective, single-blind, randomized controlled trial of 140 individuals with symptomatic knee OA. Patients will be randomly assigned into either an ITCRP group or a control group. The ITCRP group will participate in tai chi two or three times a week for 6 months. The control group will receive health education. After the 6-month intervention period, there will be a 6-month follow-up period with no active intervention in either group. The primary and secondary outcomes will be assessed at baseline, 6 months, and 12 months. Primary outcome measures will be a visual analog scale for pain, the Western Ontario and McMaster Universities Osteoarthritis Index,and the Lequesne Knee Score. The secondary outcome measures will include the Berg balance scale, knee and ankle proprioception, neuromuscular response, and 3D functional biomechanics. Furthermore, adverse events will be recorded and analyzed. If any participants withdraw from the trial, intention-to-treat analysiswill be performed.

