There are five primary types of tai chi (Yang style, Wu style, Chen style, Hao style, and Sun style), and each style takes a different approach in terms of the movements and forms. For every type of tai chi, there are many forms, such as the 24-, 36-, and 48- form Yang styles. The biomechanical characteristics, in terms of joint loading, muscle activity, and range of lower limb motion, of the tai chi movements in the intervention programs from the published studies have not been investigated. Without an understanding of tai chi biomechanics, the mechanisms of the effects of tai chi intervention for OA management would be unknown. Recently our research team has studied the biomechanical characteristics of some of the most representative tai chi movements
[10,11]. The understanding of the biomechanics of these tai chi movements gained from our studies and other published work
[12] provides the scientific basis for developing an innovative tai chi rehabilitation program (ITCRP) specifically for OA patients.

Most previous studies
[13,14] of regular tai chi programs only focus on pain relief and maintenance of the range of motionof the joint for knee OA, rarely considering the importance of neuromuscular control. Thus, it is not known whether exercise interventions influence factors associated with progression of OA. This study will not only examine the effects of a tai chi intervention on knee pain andrange of motion, but will also focus on joint biomechanics, muscle strength, proprioception tests of knee and ankle, and neuromuscular response. Hence, we aim to investigate the efficacy of a 6-month ITCRP compared with a 6-month health education program on a broad range of outcomes in patients with knee OA.

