**Figure 1 F1:**
[figure not shown]
Flow diagram of study design.

Prior to initiation of the study, all subjects will complete a questionnaire asking for details including medical history and past and present job status. Subjects will also complete the Mini–Mental State examination and the Activity of Daily Living test, and will describe their exercise habits (frequency and duration). Informed consent will be sought from all subjects prior to inclusion in the study.

The participants who meet the inclusion criteria will be allocated in a 1:1 ratio by computer-generated randomization. After randomization, participants will be assigned to either the tai chi group or the health education group (control). The study will include assessments at the following time points: before intervention, after an intervention period of 6 months, and after a further follow-up period of 6 months with no active intervention. The total study period will be 12 months.

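### The main analysis, a group × time ANOVA, does not isolate the 6-month between-arm effect and makes no use of baseline as a covariate

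*Protocol article*

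**What the plan says.** The Statistical analysis section of the protocol article describes the main efficacy comparison, for primary and secondary outcomes alike, as made "using 2-way analysis of variance (group × time"). It names no term of that model, no visit contrast and no baseline covariate. A preceding sentence adds that "Changes in variables before and after training and between groups will be analyzed", without a test. The threshold is given as "Statistical significance was assumed at *P* less than 0.05".

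The abstract fixes the visits: "The primary and secondary outcomes will be assessed at baseline, 6 months, and 12 months". It also says what separates the last two: after the 6-month intervention "there will be a 6-month follow-up period with no active intervention in either group". The Background section states the question: "we aim to investigate the efficacy of a 6-month ITCRP compared with a 6-month health education program". No section names a primary time point.

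**The concern.** The article makes a positive choice of main analysis, so this is not only detail left to an analysis plan. That choice does not line up with the aim.

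- **Interaction.** With two arms and three visits it has 2 degrees of freedom. It asks whether the profile of differences over baseline, 6 and 12 months is flat. A significant result does not say at which visit or in which direction the arms differ, and it mixes the end-of-treatment visit with one six months after treatment stopped.
- **Group main effect.** It averages the arm difference over the three visits, including baseline, where randomisation makes the expected difference zero.
- **Baseline.** It enters as one more outcome level and not as a covariate, so precision is given up.

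Two things are at stake. The headline p-value may not answer the 6-month question, which leaves the choice among interaction, main effect and a follow-up contrast open until the data are seen. And some power may be lost in a trial whose own limitations paragraph calls the sample relatively small.

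**Working it through.** **Inputs from the article.** Sample size: a "randomized controlled trial of 140 individuals with symptomatic knee OA", "allocated in a 1:1 ratio by computer-generated randomization", so n = 140/2 = 70 per arm. Alpha is 0.05. There are three visits. No assumptions accompany the 140, so there is no power figure to reproduce.

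**Assumed, because the article does not give them.** SD 1 at each visit; equal correlation ρ between visits, varied from 0.3 to 0.8; a difference d = 0.5 SD at 6 months; a share k of that difference remaining at 12 months (k = 1, 0.5 or 0); two-sided tests; complete data.

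**Formulas.** The true differences are δ = (0, d, kd) with mean δ̄. Power is from the noncentral F distribution with noncentrality λ:

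- Interaction (2 and 276 df): λ = (n/2) Σ(δ − δ̄)² / (1 − ρ), where Σ(δ − δ̄)² = d²(2 − 2k + 2k²)/3
- Group main effect (1 df): λ = (n/2) · 3δ̄² / (1 + 2ρ)
- 6-month change score (1 df): λ = (n/2) d² / [2(1 − ρ)]
- 6-month ANCOVA on baseline (1 df): λ = (n/2) d² / (1 − ρ²)

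**Step 1: does the interaction isolate 6 months?** Set the 6-month difference to zero and the 12-month difference to 0.5 SD. Then Σ(δ − δ̄)² = 0.25 × 2/3 = 0.1667. At ρ = 0.5, λ = 35 × 0.1667/0.5 = 11.67 and the rejection probability is 87%. It is 73% at ρ = 0.3 and 98% at ρ = 0.7. The test rejects readily with no 6-month effect at all.

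**Step 2: one power case in full** (ρ = 0.5, k = 0.5, so δ = (0, 0.5, 0.25) and δ̄ = 0.25).

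- Interaction: λ = 35 × 0.125/0.5 = 8.75, power 75%
- Group main effect: λ = 35 × 3 × 0.0625/2 = 3.28, power 44%
- Change score: λ = 35 × 0.25/1 = 8.75, power 84%
- ANCOVA: λ = 35 × 0.25/0.75 = 11.67, power 92%

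**Step 3: the range.** The factor (2 − 2k + 2k²)/3 is smallest at k = 0.5 (0.50) and equals 0.67 at k = 0 and k = 1. Half persistence is therefore the case least favourable to the interaction and must not be shown alone.

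| ρ | Interaction, k = 0.5 | Interaction, k = 0 or 1 | 6-month ANCOVA |
|---|---|---|---|
| 0.3 | 60% | 73% | 87% |
| 0.5 | 75% | 87% | 92% |
| 0.7 | 93.5% | 98% | 98% |
| 0.8 | 99% | 99.9% | 99.8% |

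The shortfall runs from about 27 points down to nothing. The main effect at ρ = 0.5 has power 67%, 44% and 22% for k = 1, 0.5 and 0.

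**Step 4: two levels of time only.** If the ANOVA uses only before and after training, its interaction is the 6-month change-score comparison: 84% against 92% for ANCOVA at ρ = 0.5. The variance ratio is (1 − ρ²)/[2(1 − ρ)] = (1 + ρ)/2 = 75%. Baseline adjustment still gains.

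**Step 5: sensitivity.** With 56 per arm and ρ = 0.5, the interaction has 65% (k = 0.5) or 78% (k = 0 or 1), against 86% for ANCOVA. A simulation at d = 0.474 with first-order autoregressive correlation of 0.6 gave 83%, 75% and 90% for k = 1, 0.5 and 0, against 93% to 94% for ANCOVA. The shape of the result does not depend on equal correlations.

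**The case against.** The strongest reply is that a group × time interaction is a valid randomised comparison, that no primary time point is named, and that a joint test over 6 and 12 months is therefore not off target. The section does not state that all three visits enter one ANOVA, and its mention of changes before and after training and between groups could mean two levels of time. Even with three visits, a planned 6-month contrast in the same model would answer the aim, and such detail often sits in a fuller document not shown here.

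Much of this stands. A 6-month comparison is left unspecified, not excluded. But the sentence on changes names no test and lies outside the one that defines the main analysis, so it does not settle which result answers the aim. Under the two-level reading, baseline adjustment still improves precision.

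Some stronger readings are tempting but unsupported:

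- **That the ANOVA is clearly less powerful in general.** This depends on ρ and k, which the article does not give. At high correlation with full persistence or full loss there is no meaningful shortfall.
- **That visits will be analysed as independent rows, with wrong error rates.** The model is not called repeated-measures, but group × time on the same participants is ordinary shorthand for that design, and nothing says otherwise.
- **That the group main effect is the efficacy test.** The parenthesis points to the interaction.
- **That within-arm before/after tests will serve as evidence of efficacy.** The sentence also says between groups and names no such tests.

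**Conclusion.** The point holds in a limited form. The named main analysis does not identify the 6-month between-arm difference that the Background section asks about. On the three-visit reading neither of its natural terms is that difference, and no baseline adjustment is stated. The mismatch of target does not depend on any assumed correlation: an omnibus interaction can be significant from the 12-month visit alone.

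The power cost is conditional. At 70 per arm and 0.5 SD at 6 months, the interaction against ANCOVA is 60% v 87% at ρ = 0.3 and 75% v 92% at ρ = 0.5 if half the effect remains at 12 months. The gap is about 5 points at ρ = 0.5, and about nil at ρ = 0.7 to 0.8, if the effect fully persists or vanishes. Effect size, correlation and persistence are all assumptions of this review. The ANOVA is not invalid; it leaves the primary question imprecisely tested and sometimes inefficiently so.

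**What to change.** Replace the main-analysis sentence with wording such as: *The primary analysis of each primary outcome is the between-arm difference at 6 months adjusted for the baseline value, reported with a 95% confidence interval, from ANCOVA or from a mixed model for repeated measures that accounts for within-person correlation. The 12-month between-arm difference is secondary. Changes within an arm are descriptive only.*

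If the mixed model is chosen, both contrasts come from one fit with 6 and 12 months as outcome visits and baseline as a covariate. All variables are already scheduled for collection. The cost is slightly more analysis work, and the omnibus interaction ceases to be primary, though it can still be reported as a supporting result.

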### Withdrawal criteria and management

Study patients will be allowed or asked to withdraw from the study if:

1. The participant or his or herlegal representative makes such a request.

2. The participant develops a serious disease, such as heart disease or stroke and, in the investigator’s opinion, it is not suitable to continue.

3. The participant has an adverse reaction related to the tai chi exercise program.

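### Intention-to-treat is made conditional on losses, and a tai chi reaction is a ground for leaving the study, with nothing to say that outcomes are still collected

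*Protocol article*

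**What the plan says.** The protocol article sets the rule for intention-to-treat twice, each time with a condition. The Statistical analysis section has "We will conduct an intention-to-treatanalysis if participants are lost to follow-up". The abstract (Methods/Design) has "If any participants withdraw from the trial, intention-to-treat analysiswill be performed". The triggers differ: loss to follow-up in one place, withdrawal in the other. The Statistical analysis section then explains the principle as follows: "participants in trials should be analyzed in the groups to which they were randomized, regardless of whether they received or adhered to the allocated intervention".

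The section on withdrawal criteria and management opens with "Study patients will be allowed or asked to withdraw from the study if" and gives three grounds. The third is "The participant has an adverse reaction related to the tai chi exercise program". The other two, a request by the participant or representative and a serious disease, can occur in either arm.

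On follow-up, the abstract says "The primary and secondary outcomes will be assessed at baseline, 6 months, and 12 months". No section says whether someone who withdraws for a tai chi reaction still attends the two later assessments.

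**The concern.** Intention-to-treat as the article defines it cannot depend on whether anyone is lost. It governs participants with complete data who did not adhere just as much as those who left. Adherence is likely to vary here: according to the ITCRP group section, after the first four weeks participants practise alone or in groups, keep their own practice records and are visited weekly by the instructor. Read literally, full follow-up with poor adherence would leave the article without a commitment to analyse as randomised.

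The second problem matters more, because it decides which data exist. One of the three grounds for leaving the study depends on exposure to tai chi, so it operates in one arm only and is tied to a bad experience of the intervention. If outcome collection stops at that point, analysing everyone in the randomised group becomes a promise without data behind it. The comparison would then rest on a tai chi arm from which some poor responders may have been removed.

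**Working it through.** The article has no figure to reproduce: it gives no reaction rate, dropout rate, effect size or standard deviation. The check is therefore of direction and size over an assumed range.

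**Inputs from the article.** 140 participants (Study design), allocated 1:1, so 70 per arm. Significance at P below 0.05 (Statistical analysis); two-sided is assumed, since the article does not say.

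**Assumed inputs.** d is the share of the ITCRP arm withdrawn for a reaction with no later outcome. g is how much worse, in SD, these participants would have scored than the rest of their arm.

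**Bias.** Let the remaining ITCRP participants have mean benefit m. The mean over all randomised to ITCRP is (1 − d)m + d(m − g) = m − dg. Using only those who remain gives m, so the benefit is overstated by dg.

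**Type I error.** Take a true difference of zero over all randomised, 70 controls and n₁ = 70(1 − d) remaining in the ITCRP arm. For an unadjusted comparison in SD units, SE = √(1/70 + 1/n₁), and the rejection probability is 1 − Φ(1.96 − dg/SE) + Φ(−1.96 − dg/SE).

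Example, d = 10% and g = 1: n₁ = 63, SE = √(1/70 + 1/63) = 0.174, dg/SE = 0.10/0.174 = 0.58. The probability is 0.083 + 0.006 = 0.089.

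| d | n₁ | SE | bias, g = 0.5 | type I | bias, g = 1 | type I |
|---|---|---|---|---|---|---|
| 3% | 67.9 | 0.170 | 0.015 SD | 5.1% | 0.03 SD | 5.4% |
| 5% | 66.5 | 0.171 | 0.025 SD | 5.2% | 0.05 SD | 6.0% |
| 10% | 63 | 0.174 | 0.05 SD | 6.0% | 0.10 SD | 8.9% |
| 15% | 59.5 | 0.176 | 0.075 SD | 7.1% | 0.15 SD | 13.6% |

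With g = 0 the bias is zero and the error stays at 5% for every d. A baseline-adjusted analysis with an assumed correlation of 0.5 would raise the 8.9% to 10.2%, because the SE shrinks and the bias does not; the article names no such adjustment.

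**Scale.** With 70 per arm the difference detectable at 80% power is (1.96 + 0.84) × √(2/70) = 0.47 SD. A bias of 0.03 to 0.10 SD is about 6% to 21% of that.

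**Can the analysis repair it?** A simulation of 20,000 trials took 7 of 70 ITCRP participants as 1 SD worse and all others as unaffected. The average difference was −0.10 SD over all randomised, 0.00 with the seven left out, and 0.00 with their baseline carried forward. Both substitutes hid the harm; only the measured outcomes showed it.

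**The case against.** The strongest reply has four parts.

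First, the conditional wording is loose but sets up no rival analysis. No per-protocol or as-treated population is named, and the next sentence gives the correct definition. This stands as to consequence: that limb is a wording defect, easily cured. It does not explain why a principle that always applies is given a trigger, or two different ones.

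Second, leaving the study is not shown to be automatic, since the criteria speak of being allowed or asked to withdraw. This stands too. Exit is provided for, not shown to follow every reaction, and the number affected may be small.

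Third, a reaction need not mean worse scores on the pain scale, WOMAC or Lequesne index, and reactions are recorded separately as adverse events. Controls receive lectures and are asked to avoid other rehabilitation programmes; some may leave dissatisfied, and that could offset or reverse the bias. This stands, so the direction is probable and not certain.

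Fourth, handling of missing values may lie in an analysis plan not shown. This is right for methods, and it rules out a tempting stronger reading. A reader might infer from "using 2-way analysis of variance (group × time" that withdrawn participants are dropped, because a conventional repeated-measures analysis excludes anyone with a missing visit. The article does not say so. It does not call the analysis repeated-measures, gives no deletion rule, and promises intention-to-treat in exactly this situation. Exclusion is a risk, not a stated rule. But whether outcomes are collected after the exercise stops is a matter of trial conduct. No later analysis plan can recover values that were never measured.

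**Conclusion.** The point holds as a conflict between two stated rules. Intention-to-treat is conditional where its own definition is not. A tai chi reaction is a ground for leaving the study, with nothing to keep those participants in outcome assessment. The consequence is a risk of selective loss from the ITCRP arm, likely to favour tai chi if those who react would have done worse and control-arm losses do not offset it.

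The size depends wholly on assumed rates. It is negligible to small at 3–5% withdrawn and becomes material only towards 10–15% with a gap near 1 SD. The article does not support saying that the result will be biased, or that the named analysis of variance excludes these participants. The case for acting is that the remedy is cheap, the trial status is given as recruiting, and the missing outcomes could not be restored later.

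**What to change.** (a) In the abstract and the Statistical analysis section, replace the conditional sentences with one statement: the primary analysis is by intention to treat in all randomised participants, whatever their adherence.

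(b) Reconcile the withdrawal criteria with the Statistical analysis section by separating stopping the exercise from leaving the study. Leave the clinical rule for stopping unchanged. State that participants who stop remain in the 6- and 12-month assessments unless they withdraw consent to data collection.

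The cost is wording plus outcome visits for the few who stop; those visits are already in the schedule. The estimate may come out slightly less favourable to tai chi. A different model is no substitute for (b), because someone who leaves before month 6 contributes only a baseline value under any method.

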## Discussion

Adequate and appropriate mechanical loading is an essential stimulus to maintain physiological joint homeostasis, whereas excessive mechanical stress at the joint triggers the onset and progression of knee OA. Based on joint, tissue, and movement biomechanics, tai chi is an ideal approach in the management of lower limb OA because tai chi movements are characterized by low impact, low loading rate, an accompanying neuromuscular training effect, and a specific gentle gait pattern
[36]. The highest knee joint reaction forces when performing tai chi movements are equivalent to only 1.2 times body weight
[12], significantly less than the joint reaction force when walking (3 times body weight)
[37]. The special tai chi stepping pattern, characterized by multidirectional foot movements with gentle foot landings, may provide good gait training for patients with knee OA
[31,38]. Tai chi is also a low-cost exercise that can be performed at home without the use of any special equipment.

However, findings of studies on tai chi for OA are very difficult to compare because tai chi intervention programs differ in terms of duration, style, and movements. Some tai chi styles and movements are difficult for older people to learn, and not all tai chi styles and movements are suitable for knee OA.

### Strengths and limitations

Firstly, the proposed research program is unique in that the ITCRP intervention is specifically designed for subjects with knee OA. Secondly, the study duration is relatively long, with an intervention period of 6 months and a follow-up period (with no active intervention) of 6 months, giving a total study period of 12 months. Previous tai chi intervention studies have typically ranged in duration from a few weeks to six months
[39]. Thirdly, we will use a full three-dimensional biomechanical analysis to determine the mechanism by which kinematics and kinetics of the joints change during intervention and provide a quantitative analysis of the effect of intervention. The impact of tai chi on joint biomechanics remains unclear. Previous studies have focused on knee range of motion, knee pain, joint stiffness, walking speed, and stride length, but three-dimensional joint biomechanics of patients with OA has not yet been analyzed. Published studies have suggested that gait assessment without full three-dimensional analysis provides only limited information on the level of joint impairment and limits the development of rehabilitation strategies
[40]. Limitations of this pilot study are the relatively small sample size (only 140 subjects) and the fact it is not a multicenter trial. In addition, owing to the limited numbers of subjects, we will not compare the efficacy of ITCRP with a regular tai chi program or any other exercise.

In conclusion, this study aims to develop an ITCRP for patients with knee OA, and to estimate the effect of ITCRP intervention on outcomes including pain, function, balance, and joint biomechanics in knee OA. The results of the proposed study will provide a good foundation from which to develop new biomechanics-based exercise therapies for patients with knee OA. Based on the results of the proposed project, further comprehensive research on exercise rehabilitation of knee OA will be proposed.

